### Planned subgroup analysis

Subgroup analyses will be performed to assess the impact of demographic factors, including gender, age, type of children’s caregivers (e.g., parents, grandparents, others), education level of caregivers, and household income per capita per month. Subgroup analyses will follow primary analyses.

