### Sample size

Sample size was calculated based on our primary hypothesis, to detect a difference between the intervention and control groups in unintentional injury incidence among preschoolers in the prior 3 months. Previous studies reported an unintentional injury incidence of 25.5% among preschoolers in central China in the past 1 year [22] and an effect size of 0.64 between intervention and control groups [23]. Considering 1 year recall periods underestimate injury rates by 55 and 72% (most are minor injuries) compared with one-month recall periods [24, 25], and use of a strict operational definition that restricts injury events to those that cause activity restriction of 1 day or longer or are treated by a doctor or other medical professional substantially undercounts injury events (typically minor or moderate injuries) [26], we assume unintentional injury incidence among preschoolers in the past 3 months will be 23%. On the basis of a previous report [27], we estimate an intra-class correlation (ICC) of 0.005 within a preschool of 140 students. Predicting an incidence of 23% in the control group, an effect size of 0.75 between intervention and control groups, and an ICC of 0.005, α = 0.05, 1-ß = 0.80, a minimum sample size of 1181 caregivers is needed for each group. Conservatively estimating an attrition rate of 10% in the six-month follow-up study, we will require a recruited sample size of 1323 each group. In total, therefore, we will enroll 2626 participants. Since most preschools have far more than 100 students enrolled, 20 preschools are amply sufficient to recruit the needed sample size.

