### Data analysis plan

Analysis will follow the intention-to-treat approach [38]. Descriptive data (mean, standard deviation, median, inter-quartile range, proportion) will be calculated to describe the characteristics of primary and secondary outcome measures and covariates. Chi-square test (categorical outcomes) and two sample independent *t*-test (continuous outcomes) will examine differences in unintentional injury incidence and other outcome indicators between the two arms at each time point (baseline, 3 months, 6 months). Chi-square test (categorical outcomes) and analysis of variance for repeated measurement data (continuous outcomes) will detect differences across the three time points for each arm.

The primary analysis will be conducted through Generalized Estimation Equation (GEE) models, which will test the effectiveness of the app-based intervention based on the interaction of group (intervention vs. control) with time (baseline, 3 months, 6 months) after adjusting for socio-demographic variables (age, sex, household income) and compliance to the intervention (use of the app-based interventions).

Missing values will be imputed using the Expectation Maximization algorithm (EM). To test the robustness of results, sensitivity analysis will be conducted by comparing primary and secondary outcome data collected through the online app-based survey and those completed using a printed questionnaire survey. Statistical analysis will be performed through Stata/IC 12.1. Statistical significance will be based on 2-sided tests at the level of 0.05.

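### The subgroup plan aims to assess the impact of five demographic factors but, as most naturally read, tests for an effect within each level and never compares levels

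*Protocol article*

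**What the plan says.** Under Planned subgroup analysis, the aim is "Subgroup analyses will be performed to assess the impact of demographic factors, including gender, age, type of children’s caregivers", followed by caregiver education and household income. That makes five factors. The only statement of method is "Subgroup analyses will follow primary analyses".

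Under Data analysis plan, the primary analysis is a GEE that will "test the effectiveness of the app-based intervention based on the interaction of group (intervention vs. control) with time (baseline, 3 months, 6 months", adjusted for socio-demographic variables and compliance. The significance rule is general: "Statistical significance will be based on 2-sided tests at the level of 0.05".

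Group by time is the only interaction that the article names. It represents the intervention effect itself. Age, sex and household income also enter the primary model, but as adjustment variables, which says nothing about whether the effect varies with them.

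**The concern.** To assess whether a factor matters for the intervention effect, the null hypothesis has to be that the effect is equal across the factor's levels. Refitting the primary model within boys and within girls, or within parents and within grandparents, tests a different null: no effect in this level. No term in those fits compares one level with another.

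Such output invites the reader to contrast a significant level with a non-significant one. Each level holds only part of the sample, so each test has much less power than the whole trial. One level can then easily succeed while the other fails, even though the true effect is the same in both. At stake is what the trial reports about who benefits by sex, age, caregiver type, education or income. The overall test of the app is not at stake.

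**Working it through.** **Inputs from the article.** Sample size: "Predicting an incidence of 23% in the control group, an effect size of 0.75 between intervention and control groups"; "we estimate an intra-class correlation (ICC) of 0.005 within a preschool of 140 students"; "an ICC of 0.005, α = 0.05, 1-ß = 0.80, a minimum sample size of 1181 caregivers is needed for each group". School recruitment: 10 preschools per arm. Data analysis plan: two-sided 0.05. The effect size is read as a risk ratio, so 0.75 × 23% = 17.25% in the intervention arm. The article gives no subgroup shares; I assume 50:50 and vary this to 20:80.

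**The plan's own figure first.** Two proportions, 23% v 17.25%, two-sided 0.05, 80% power: 763 per arm before clustering. Design effect = 1 + (m − 1) × ICC.

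- m = 140: 1 + 139 × 0.005 = 1.695, giving 1,294 per arm. The stated 1,181 is not reproduced.
- m = 118 (1,181 / 10 preschools): 1.585, giving 1,210, within 3% of 1,181.
- Power at 1,181 per arm: 76.4% with m = 140, 79.1% with m = 118.

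I use m = 118 below. With m = 140, the 50:50 result is still 49–50%.

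**Power in each half, same risk ratio of 0.75 in both.** Each half has 1,181 / 2 = 590.5 per arm.

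- Design effect recalculated for about 59 per school: 1 + 58.05 × 0.005 = 1.290. Effective n = 590.5 / 1.290 = 458; power 58.3%.
- Full design effect kept: 590.5 / 1.5855 = 372; power 49.9%.

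**Exactly one level significant.** With powers a and b and the two tests treated as independent, the probability is a(1 − b) + b(1 − a).

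| Split | Powers (design effect recalculated) | Exactly one | Powers (full design effect) | Exactly one |
|---|---|---|---|---|
| 50:50 | 58.3%, 58.3% | 48.6% | 49.9%, 49.9% | 50.0% |
| 30:70 | 42.2%, 69.1% | 53.0% | 32.8%, 63.9% | 54.8% |
| 20:80 | 31.4%, 73.1% | 58.6% | 23.5%, 69.7% | 60.5% |

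**Checks on the approximation.**

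- The two levels share schools, so their tests are not quite independent. A cluster simulation (10 schools of 118 per arm, ICC 0.005, t-tests on school proportions, 4,000 runs) gave 42–44% for a 50:50 factor.
- The primary term is a change from baseline. For a baseline-to-follow-up contrast with assumed within-child correlation ρ, the noncentrality is 2.80 / √(2(1 − ρ)), times √0.5 in each half. At ρ = 0: power 28.8% per half, exactly one 2 × 0.288 × 0.712 = 41%. At ρ = 0.5: power 50.8%, exactly one 50%.
- A simulation of 500 trials with three time points and a school-clustered logistic group-by-time test gave 51%.

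The range for one two-level factor is therefore about 41–61% at the design effect.

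**How it depends on the true effect.** If the true effect gives the whole trial only 20% power, each half has 12.1%, and exactly one is significant in 2 × 0.121 × 0.879 = 21%. With no effect it is 2 × 0.05 × 0.95 = 9.5%; simulations gave 9–9.5%.

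**Direct interaction test.** In the cluster simulation, testing the between-level difference in effect rejected in 4.9% of trials per factor. At least one of five independent factors was rejected in 22.3%, against 1 − 0.95⁵ = 22.6%.

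**The case against.** The strongest reply is that the article never says the primary model will be refitted in each subgroup. The verb in the method sentence could simply mean that subgroup analyses come afterwards. The article would then state no subgroup method, and a journal article may leave that to an analysis plan that is not shown. Even on the same-method reading, adding factor terms to the full-sample GEE would also be following the primary analysis. Nor does any sentence say that a level will be declared to benefit, or not, from its own p-value; stratified estimates and intervals could properly be compared.

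Much of this stands. Separate refitting is an inference, and the contrast of p-values is a rule that a reader might apply, not one the article states. A reader might also infer that a uniform benefit will look subgroup-specific in about half of all trials. The documents do not support that unconditional claim: it needs the refitting, the contrast of p-values, a true effect near the design value and assumed subgroup shares. The Discussion foresees wide dissemination and proposes no targeting by subgroup, so misdirected rollout is not a consequence the article sets up.

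The reply does not dispose of the point. Where the article elsewhere says that an analysis will follow something (intention to treat in the Data analysis plan, NICE guidance under Secondary outcome measures), it means method and not sequence. The Data analysis plan also already tests each arm separately across time. On that reading the article fixes a method that does not answer its own aim, which is more than an omitted detail.

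**Conclusion.** The point holds in conditional form. On the most natural reading, the stated method tests for an effect within each level and contains no comparison between levels, so it cannot answer the stated aim. If levels are contrasted by their own p-values, a uniform risk ratio of 0.75 would appear confined to one level of a single two-level factor in roughly 40–60% of trials, against about 5% with a direct test. The figure assumes about 118 analysed caregivers in each of 10 schools per arm, ICC 0.005, and splits from 50:50 to 20:80. It falls to about 21% when overall power is 20%, and to about 9% with no effect.

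The primary conclusion does not depend on this. Severity is low and the improvement is cheap.

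**What to change.** In Planned subgroup analysis, replace the method sentence with wording to this effect: Effect modification by each of the five factors will be tested in the full-sample primary GEE by adding the factor and its interaction with the intervention effect (factor by group by time), with the same handling of preschool clustering. Subgroup effects will be shown as estimates with 95% confidence intervals and will not be judged by their own p-values. The five interaction tests are exploratory.

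This resolves either reading of the present sentence. It costs a few lines of text and one set of model terms per factor, with no new data. The downside is that interaction tests have low power, so most will be inconclusive. With five tests at 0.05, about 22% of trials with a uniform effect would still show at least one nominally significant interaction, which is why the exploratory label is needed.

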## Discussion

Smartphone apps are emerging as an effective, low-cost platform to disseminate health and safety information [39, 40]. They offer great potential for injury prevention, particularly in countries and regions where injury control resources are limited but smartphone penetration is high.

This trial is designed to evaluate the effectiveness of an app-based intervention to prevent unintentional injuries to preschool-aged children in Changsha, China. The app-based intervention targets caregivers by educating them about the most common unintentional injury causes for Chinese preschoolers. It is developed based on relevant theories [28–30], empirical research evidence, and a systematic needs assessment, and it is anticipated that it will result in both knowledge acquisition and behavior change on the part of the caregivers. Unlike most published trials, it will use injury incidence as the primary outcome measure.

We also will conduct economic analyses to demonstrate the cost benefit of the app. If our hypotheses prove true, we anticipate the app could be readily and cost-effectively disseminated across China, yielding substantial public health benefit by reducing unintentional injuries among preschoolers [12].

## Abbreviations

CONSORT: Consolidated standards of reporting trials
EM: Expectation maximization algorithm
FAQs: Frequently asked questions
GEE: Generalized estimation equation
HICs: High-Income Countries
ICC: Intra-class correlation
ICD-10: International statistical classification of diseases and related health problems 10th revision
ICERs: The incremental cost and effectiveness ratios
mHealth: Mobile health
NICE: National institute for health and clinical excellence
SPIRIT: Standard protocol items: recommendations for interventional trials
